### Secondary analysis

Repeated measures of each of the primary outcomes (at 6, 24, 48, 72 hours, 6 weeks, 6 months and 1 year) will be modelled using multi-level mixed-effects linear regression models. The assumption of approximate normality of the residuals will be assessed graphically. These models will use repeated measures (level 1) nested within participants (level 2) and will include a random effect to account for heterogeneity in response due to recruitment centre (level 3). The models will also include fixed effects for type of surgery (TKR versus UKR), baseline values, age, gender and, in the case of the pain scores, use of pre-operative opiate pain medication. Time will be treated as categorical and interactions between treatment and time will be included in the model to allow for treatment effects to vary over the follow-up. The adjusted difference between treatment groups (and associated 97.5% confidence interval) will be reported (see Table 11). This analysis will be conducted for the ITT population (see Section 4.2).

If, in either case, approximate normality of the residuals is not appropriate, the first approach will be to consider a transformation of the data. If approximate normality cannot be achieved by transformation, the data will be analysed separately at each time point using a non-parametric equivalent with no adjustment. Medians and inter-quartile ranges will be reported for each treatment group.

In addition, a summary measures approach to cumulative pain will also be used as a supporting analysis for this outcome. For each participant, cumulative pain score from 6 to 72 hours post-surgery will be calculated as the area under the curve. Participants with missing pain scores at either 6 or 72 hours will be excluded from this analysis. The potential impact of missing data will be investigated separately. Pain score AUCs will be summarised by treatment group using unadjusted means and associated SDs (Table 11). A multivariate linear regression will be used to compare the AUCs between the treatment groups, adjusted as described previously. The adjusted difference (97.5% CI) and associated p-value will be presented (Table 11).

**Table 11:** Secondary analysis of primary outcomes (ITT population)

|          |                      | Intervention |           | Control |           | Adjusted diff | p-value |
|----------|----------------------|--------------|-----------|---------|-----------|---------------|---------|
|          |                      | n            | mean (SD) | n       | mean (SD) | (97.5% CI)    |         |
| QoR-40   | 6 hours              | X            | X (X)     | X       | X (X)     | X (X, X)      | X       |
|          | 24 hours             | X            | X (X)     | X       | X (X)     | X (X, X)      | X       |
|          | 48 hours             | X            | X (X)     | X       | X (X)     | X (X, X)      | X       |
|          | 72 hours             | X            | X (X)     | X       | X (X)     | X (X, X)      | X       |
|          | 6 weeks              | X            | X (X)     | X       | X (X)     | X (X, X)      | X       |
|          | 6 months             | X            | X (X)     | X       | X (X)     | X (X, X)      | X       |
|          | 1 year               | X            | X (X)     | X       | X (X)     | X (X, X)      | X       |
| Pain VAS | 6 hours              | X            | X (X)     | X       | X (X)     | X (X, X)      | X       |
|          | 24 hours             | X            | X (X)     | X       | X (X)     | X (X, X)      | X       |
|          | 48 hours             | X            | X (X)     | X       | X (X)     | X (X, X)      | X       |
|          | 72 hours             | X            | X (X)     | X       | X (X)     | X (X, X)      | X       |
|          | 6 weeks              | X            | X (X)     | X       | X (X)     | X (X, X)      | X       |
|          | 6 months             | X            | X (X)     | X       | X (X)     | X (X, X)      | X       |
|          | 1 year               | X            | X (X)     | X       | X (X)     | X (X, X)      | X       |
| Pain VAS | Summary measures AUC | X            | X (X)     | X       | X (X)     | X (X, X)      | X       |

## Secondary outcomes

Continuous outcomes (OKS and AKSS) will be summarised over time (from baseline to 12 months post-randomisation) by treatment groups using boxplots and will be analysed using similar methods to those outlined for the secondary analysis of the primary outcomes. Multi-level, mixed-effects linear regression

models analogous to those described previously will be used. The assumption of approximate normality of the residuals will be assessed graphically. The adjusted difference between treatment groups (and associated 95% confidence interval) will be reported (see Table 12).

Cumulative opiate use will be approximately continuous; however, it is unlikely to be normally distributed. As described above the possibility of transformation to achieve approximate normality will be considered. If normality can be achieved linear regression will be used as previously described. If this cannot be achieved a non-parametric analysis with no adjustment will be used. The results will be summarised as outlined in Table 12.

**Table 12:** Analysis of continuous secondary outcomes

| Scale                 |          | Intervention           |   | Control                |   | Adjusted diff (95% CI) | p-value |
|-----------------------|----------|------------------------|---|------------------------|---|------------------------|---------|
|                       |          | Mean (SD)  | N | Mean (SD)  | N |                        |         |
| OKS                   | 6 weeks  | X (X)                  | X | X (X)                  | X | X (X,X)                | X       |
|                       | 6 months | X (X)                  | X | X (X)                  | X | X (X,X)                | X       |
|                       | 1 year   | X (X)                  | X | X (X)                  | X | X (X,X)                | X       |
| AKSS - Expectations   | 6 weeks  | X (X)                  | X | X (X)                  | X | X (X,X)                | X       |
|                       | 6 months | X (X)                  | X | X (X)                  | X | X (X,X)                | X       |
|                       | 1 year   | X (X)                  | X | X (X)                  | X | X (X,X)                | X       |
| AKSS - Satisfaction   | 6 weeks  | X (X)                  | X | X (X)                  | X | X (X,X)                | X       |
|                       | 6 months | X (X)                  | X | X (X)                  | X | X (X,X)                | X       |
|                       | 1 year   | X (X)                  | X | X (X)                  | X | X (X,X)                | X       |
| AKSS - Function       | 6 weeks  | X (X)                  | X | X (X)                  | X | X (X,X)                | X       |
|                       | 6 months | X (X)                  | X | X (X)                  | X | X (X,X)                | X       |
|                       | 1 year   | X (X)                  | X | X (X)                  | X | X (X,X)                | X       |
| Cumulative opiate use |          | X (X)                  | X | X (X)                  | X | X (X,X)                | X       |

Or Median (IQR)

Fitness for discharge is a binary variable. The number and percentage of patients fit for discharge at days 0, 1, 2 and 3 following surgery will be summarised by treatment group (see Table 13). Any instances where someone is fit for discharge at one time point and not at some subsequent one will be summarised. The two treatment groups will be compared using a multi-level logistic regression model with repeated measures (level 1) nested within participants (level 2) and adjusted for recruiting centre as a random effect (level 3). The model will also be adjusted for type of knee replacement, age and gender as fixed effects. Time will be included as a categorical covariate and a treatment-by-time interaction will be included. Adjusted ORs and associated 95% confidence intervals will be reported at each time point (see Table 13). Unadjusted ORs will also be calculated.

Fitness for discharge and actual discharge status will also be summarised by treatment group at each time point (see table 14). Reasons for discrepancies will also be summarised. The average lengths of time from surgery to being determined fit for discharge and from being determined fit for discharge to being discharged will be summarised by treatment group using medians and IQRs.

**Table 13:** Analysis of secondary outcomes (categorical)

|                       |       |  | Intervention |   | Control |   | Difference (95% CI) |         |
|-----------------------|-------|--|--------------|---|---------|---|---------------------|---------|
|                       |       |  | N            | % | N       | % |                     |         |
| Fitness for discharge | Day 0 |  | X            | X | X       | X | X (X,X)             | X (X,X) |
|                       | Day 1 |  | X            | X | X       | X | X (X,X)             | X (X,X) |
|                       | Day 2 |  | X            | X | X       | X | X (X,X)             | X (X,X) |

|                      |                     |   |   |   |   |         |         |
|----------------------|---------------------|---|---|---|---|---------|---------|
|                      | Day 3        | X | X | X | X | X (X,X) | X (X,X) |
| Complications | N overall    | X | - | X | - | -       | -       |
|                      | Participants | X | X | X | X | X (X,X) | X (X,X) |

**Table 14:** Comparison of fitness for discharge and actual discharge status

|              |                              | Intervention (n, %) |                       | Control (n, %) |                       |
|--------------|------------------------------|----------------------------|-----------------------|-----------------------|-----------------------|
|              |                              | Discharged          | Not discharged | Discharged     | Not discharged |
| Day 0 | Fit for discharge     | X (X)                      | X (X)                 | X (X)                 | X (X)                 |
|              | Not fit for discharge | X (X)                      | X (X)                 | X (X)                 | X (X)                 |
| Day 1 | Fit for discharge     | X (X)                      | X (X)                 | X (X)                 | X (X)                 |
|              | Not fit for discharge | X (X)                      | X (X)                 | X (X)                 | X (X)                 |
| Day 2 | Fit for discharge     | X (X)                      | X (X)                 | X (X)                 | X (X)                 |
|              | Not fit for discharge | X (X)                      | X (X)                 | X (X)                 | X (X)                 |
| Day 3 | Fit for discharge     | X (X)                      | X (X)                 | X (X)                 | X (X)                 |
|              | Not fit for discharge | X (X)                      | X (X)                 | X (X)                 | X (X)                 |

The total number of complications experienced will be summarised by treatment group, as well as the number of participants experiencing at least one complication. The number of participants experiencing a complication will be compared using a logistic regression model adjusted as outlined previously (see Table 13). Descriptive data on the types of complications experienced, Clavien-Dindo classification of complications and timing of complications will also be presented.

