## 6.2. Number of Centres

Participants will be recruited from approximately 10 NHS hospitals throughout the United Kingdom. The number of recruiting centres may be increased as the study progresses. Any additional sites will be added via a notification of amendment form to the REC and HRA, following approval by the Sponsor.

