### **8.3. Randomisation, Blinding and Code-breaking**

Randomisation will be performed locally by the trial site using a secure online internet based system (RRAMP) provided by the Oxford Clinical Trials Research Unit (OCTRU).

Patients will be randomised 1:1 to the two treatment groups using stratified randomisation with variable block sizes, stratified by trial hospital and surgical procedure (TKR or UKR).

Due to local patient pathways, informed consent and baseline assessments may be completed at the same hospital visit however, it may be the case randomisation is not performed on the same day. Where possible, randomisation will occur on the day of surgery either by a member of the clinical research team or a member of the surgical team, where this is not possible randomisation may occur on the days prior to surgery to allow for time to coordinate the drug supplies and inform the operative and anaesthetic team. If consent has occurred more than a day before randomisation, the local research team will verbally check the patient still agrees to participation before proceeding with randomisation.

Only trial team members listed on the delegation log are authorised to perform randomisations.

Patients will be blinded to the treatment allocation. Trial sites should make every effort to ensure that patient blinding is maintained throughout the duration of the trial so that no bias is introduced. The arrangements for maintaining patient blinding for the trial should be considered in detail and those arrangements carefully planned, documented and communicated to ensure accidental unblinding is avoided.

Methods for ensuring patient blinding should be discussed during the Site Initiation Visits, and may include only recording the drug given (active/control) in the surgeon notes as "as per protocol of SPAARK trial" but the actual drug given recorded in the anaesthetic chart. Local practice may vary and the trial sites can discuss with the central study team alternative ways to ensure that patient blinding is maintained.

Unblinding will be performed on an individual basis as clinical need dictates.

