#### 9.6.1. Post-Operative Analgesia

Post-operative opioid consumption will be captured on the In-patient CRF. The management of post-operative pain may vary across each participating centre. Local post-operative analgesic regimes must be discussed and approved by the Chief Investigator prior to site activation.

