#### 3.2 Randomisation and Blinding

Randomisation between intervention and control will be 1:1, and will be stratified by study centre and operation type (Total Knee Replacement (TKR) or Unicompartmental Knee Replacement (UKR)). Randomisation will be performed using the RRAMP internet system provided by the Oxford Clinical Trials Research Unit (OCTRU). Where possible, randomisation will occur in theatre at the time of surgery either by a member of the clinical research team or a member of the surgical team. If not possible, randomisation can occur on days prior to the surgery to allow for time to coordinate the drug supplies and inform the operative and anaesthetic team. If consent has occurred more than a day before randomisation, the local research team will verbally check the patient still agrees to participation before proceeding with randomisation.

Full details of the randomisation are available in SPAARK\_RBP\_v3.0\_19Apr2018, stored in the confidential statistical section of the TMF.

The patient will be blinded to the treatment allocation. Unblinding will be performed on an individual basis as clinical need dictates. Surgeons who administer the medication cannot be blinded to treatment allocation; however, blinding of surgeons and outcome assessors is not necessary as the two co-primary outcomes are patient reported measures.

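### If no transformation normalises cumulative opiate use, the SAP's unadjusted non-parametric fallback ignores the randomisation strata: still valid, but conservative if centres differ, and unable to fill Table 12

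*Combined protocol and SAP*

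**What the plan says.** Under Secondary outcomes, SAP 6.2 Analysis Methods gives cumulative opiate use a three-step rule.

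1. It states an expectation: "Cumulative opiate use will be approximately continuous; however, it is unlikely to be normally distributed".
2. It puts transformation first: "As described above the possibility of transformation to achieve approximate normality will be considered". On success, "If normality can be achieved linear regression will be used as previously described". The models described earlier in 6.2 include recruitment centre and type of surgery.
3. Failing that: "If this cannot be achieved a non-parametric analysis with no adjustment will be used". No test and no effect estimate are named.

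Table 12 nevertheless gives this outcome an adjusted-difference column with a 95% CI. The table's footnote allows medians and IQRs in place of means and SDs in the group summary columns only; it offers nothing in place of the adjusted difference.

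On the design, SAP 3.2 says: "Randomisation between intervention and control will be 1:1, and will be stratified by study centre and operation type". Protocol 8.3 describes "stratified randomisation with variable block sizes, stratified by trial hospital and surgical procedure (TKR or UKR"). Protocol 6.2 adds: "Participants will be recruited from approximately 10 NHS hospitals throughout the United Kingdom". Protocol 9.6.1 says: "The management of post-operative pain may vary across each participating centre". Local regimes need the Chief Investigator's approval before a site opens, but no common regime is imposed.

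**The concern.** Blocked randomisation within centre and operation type balances the arms on those factors. An analysis that then ignores them treats between-centre differences in opioid totals as chance variation between the arms, which the design has largely removed. The standard error is too large for the design, the p-value tends to be too large, and power is lost.

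Opioid use is the outcome on which local analgesic practice acts most directly. The SAP's models for the primary outcomes and for fitness for discharge all carry centre, so the fallback departs from the SAP's own approach where centre may matter most. Reducing opioid use is central to the protocol's rationale (section 4), so a missed effect here would weaken the supporting evidence.

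A second problem needs no assumption about centres: once the fallback is taken, the last columns of Table 12 have no defined content, and the analyst must choose an estimate after seeing the data.

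**Working it through.** **The plan's own figures.** The documents give no power for opioid use, only for the two primary endpoints. With n per arm = 2(z₁₋α/₂ + z_power)²(SD/difference)², α = 0.025 and 90% power:
- QoR-40 (difference 5, SD 15.5): 239, against 240 stated.
- Pain AUC: 228 for a standardised difference of 0.33, or 224 for 1/3, against 225 stated.
- Both are inflated to 250 per arm (240/0.96 and 225/0.90).

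So 500 patients is the right base.

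**Inputs from the documents.** 500 patients, 1:1; about 10 centres; strata of centre and operation type; variable block sizes; UKR at most 10%; α = 0.05 for secondary outcomes (SAP 4.1), taken as two-sided.

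**Assumptions, not in the documents.** The between-centre share of variance on the log scale (written ICC), varied from 0 to 30%; blocks of 2, 4 and 6; a within-centre shift of 0.26 or 0.30 SD; skewed totals with some values tied at the floor.

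**Closed form, perfect balance within centre.** The unadjusted test scales by the total variance, 1, but under the design its statistic varies only with the within-centre part, 1 − ICC. Hence

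true type I error = 2Φ(−1.96/√(1 − ICC)).

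If the stratified test has power Φ(θ − 1.96), the unadjusted test has power Φ(θ − 1.96/√(1 − ICC)). For 79% stratified power, θ = 1.96 + 0.806 = 2.766. At ICC 20%, 1.96/√0.8 = 2.191, so type I error is 2Φ(−2.191) = 2.8% and power is Φ(0.575) = 72%.

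**Simulations, unadjusted rank-sum test against van Elteren.**
- A: 10 centres of 20 to 90 patients, strata = centre, a few tied low values, shift 0.26 SD; 4,000 null and 3,000 power runs.
- B: strata = centre by operation type, 5% zeros, shift 0.30 SD; 8,000 null and 4,000 power runs. Simulation error is about 0.2 points on type I error and 0.6 to 0.7 on power.
- C: as a check on data that would plausibly defeat transformation, 30% of values tied at the floor.

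| ICC | Type I error, unadjusted: closed form / A / B / C | Power, A: unadjusted v stratified | Power, B: unadjusted v stratified | Power loss in C, points |
|---|---|---|---|---|
| 5% | 4.4 / – / 4.3 / – % | – | 83.0 v 82.8% | 1 or less |
| 10% | 3.9 / 3.9 / 4.0 / 4.2 % | 77 v 79% | 81.0 v 82.2% | about 3 |
| 20% | 2.8 / 3.1 / 3.5 / 3.2 % | 74 v 79% | 76.2 v 81.5% | about 6 |
| 30% | 1.9 / 2.4 / 3.0 / 2.8 % | 68 v 78% | 73.0 v 82.7% | about 10 |

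The stratified test stayed near 5% in A and B (4.7% to 5.3% over these shares). The closed form gives power of 76%, 72% and 66% at ICC 10%, 20% and 30%, against 79%. That is a limiting case; I rely on the simulations, which allow for unfinished blocks and ties.

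**Cost of stratifying when centres do not differ.** In A at ICC 0, power is 79% stratified against 80% unadjusted. In B at ICC 2%, both are about 83%.

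**Table 12.** An analysis with no adjustment yields no adjusted difference. This follows from the text alone.

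**The case against.** The strongest reply is that the plan's first choice already does what is asked. Non-normality of the raw totals is the reason to transform, not a forecast that transformation will fail, and success leads to a regression with centre and type of surgery. In simulated log-normal data with 5% of values at the floor, log-scale regression with centre terms held about 80% to 83% power at every between-centre share from 0 to 30%. This stands: the loss arises only in the fallback. A reader might infer from the SAP that opioid use goes straight to an unadjusted test; it does not. But transformation is only something to be considered, and the pattern persisted with 30% of values at the floor, where transformation would plausibly fail.

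Second, materiality rests on an assumed variance share. This also stands. A reader might infer that regimes do differ; the protocol says only that they may, and requires central approval. At a 5% share there is essentially no loss.

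Third, one might equate the loss with discarding the same share of patients as the between-centre share, 10% to 30%. The figures do not support that. With n proportional to (1.96 + z_power)², simulation A at 10% gives 1 − (2.699/2.766)² = 5%. The corresponding losses at 20% and 30% are about 11% and 21% to 23%; simulation B gives about 3%, 12% and 21%.

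Fourth, an unadjusted fallback is a convention applied throughout the SAP, and it is valid here: its type I error does not exceed 5% beyond simulation error, so it cannot manufacture a finding. True; the change improves efficiency and completes the specification rather than repairing an invalid test. SAP 6.2 names no rank test either, though that is the natural reading.

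**Conclusion.** The point holds as a conditional one. If transformation fails, the fallback ignores both stratification factors and is conservative to the extent that centres differ. Under assumed between-centre shares of 5%, 10%, 20% and 30%, type I error is about 4% to 5%, 4%, 3% to 3.5% and 2% to 3%, and power falls by about 0 to 1, 1 to 3, 5 to 6 and 10 points. It is material only at about 20% or more, and the documents do not say where the trial lies. The mismatch with Table 12 holds whatever the share.

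The documents do not support a claim of false-positive risk, or of any effect on the primary conclusions: this is a secondary outcome, which SAP 4.1 treats as supporting. The change is still worth making because it costs almost nothing and removes a choice of test and estimate left open until the data are seen.

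**What to change.** In SAP 6.2, keep the transformation step and the adjusted regression. Replace the fallback for cumulative opiate use with a van Elteren rank test stratified by centre and operation type, stating in advance the minimum UKR number below which UKR is pooled with TKR within a centre. Pooling will be needed: at most 10% of 500 is 50 UKR patients, or about 5 per centre over 10 centres.

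Name one matching estimate, a stratified Hodges-Lehmann difference with its 95% CI, and add a Table 12 footnote saying that this fills the difference column when the fallback is used.

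Cost: one sentence, one footnote and a few lines of code, with no new data. Downside: very small strata add little information, and if centres do not differ, at most about 1 point of power is lost.

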## 6.3. Patient Participation

Patients will be involved for a maximum of 12 months post-randomisation. Post operatively, patients will be asked to complete Quality of Recovery-40 assessment daily and a visual analogue scale (VAS) pain score 0-10 on the evening of surgery (day 0) and on days 1, 2 and 3 following surgery. The analgesia requirements of each patient will be recorded. The time of surgery for the patient will be noted. The day of surgery will be called Day 0.

If the patients are discharged home prior to 72 hours postoperatively, then a phone call will be made daily to the patient to collect pain VAS and QoR-40. Pain VAS will be collected by asking the question 'How painful has your operated knee been over the past 24 hours on a scale of 0-10?' The EQ-5D-5L section of the questionnaire will also be completed over the telephone if deemed appropriate. If the patient cannot be contacted between those hours, then an additional call will be made between 2pm and 6pm and this will be noted.

Fitness for discharge will be assessed as per routine clinical care on the evening of surgery (day 0) day 1, 2 and 3 following surgery, until the patient is deemed fit for discharge. This is assessed against the following criteria:

- Ability to mobilize independently
- Pain score less than or equal to 3cm on a 10cm VAS

- Ability to straight leg raise
- Ability to bend knee to 90 degrees

Once discharged, patients will be assessed as per routine clinical care. The Central Study Office will post questionnaires to patients for completion at 6 weeks post-surgery, and at 6 months and 1 year following randomisation. The local hospital research team should encourage timely completion of questionnaires if these time points coincide with the routine follow up appointments. Assessments will include completing the Quality of Recovery 40, Oxford Knee Score, American Knee Society Score and EQ-5D-5L. In addition, an analgesic history will be taken.

A trial flowchart is provided in appendix A.

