## 6. ANALYSIS

### 6.1 Outcome Definitions

The **co-primary outcome measures** in this trial are the Quality of Recovery 40 score and the cumulative daily pain score both measured at 72 hours post-surgery.

Quality of Recovery (QoR) 40 score – a five dimension validated patient reported peri-operative recovery score that has been widely used across a range of surgeries including knee replacement and assesses overall post-operative recovery [19]. It consists of 40 items each of which is graded on a five-point Likert scale. Total scores are calculated by summing the individual items. QoR-40 scores range from 40 (extremely poor quality of recovery) to 200 (excellent quality of recovery) [18]. The primary time point will be 72 hours post-surgery.

This outcome will also be measured at 6, 24 and 48 hours post-surgery and at 6 weeks, 6 and 12 months post-randomisation.

Cumulative daily pain score – pain at rest will be measured using a visual analogue scale (VAS) ranging from 0 (no pain) to 10 (worst possible pain). Measurements taken as close as possible to 6, 24, 48, and 72 hours post-surgery will be included in the primary outcome assessment. This outcome will also be measured at 6 weeks, 6 and 12 months post-randomisation.

The **secondary outcome measures** in this trial are cumulative opiate use, the Oxford Knee Score, the American Knee Society Score, fitness for discharge, and the co-primary outcome measures at additional time points. The health economics outcomes in this trial include summary medication history, EQ-5D-5L, summary healthcare and social services use, and summary employment history.

Cumulative opiate use – all opioids used on evening of surgery (day 0) and days 1, 2, and 3 will be recorded and a running total of cumulative opioid use calculated. A list of acceptable opioids is provided in the trial protocol.

Fitness for discharge – this will be assessed against pre-defined criteria on evening of surgery (day 0) and days 1, 2, and 3 following surgery as per routine clinical care. Patients will be considered fit for discharge when they meet four criteria: (i) ability to mobilise independently; (ii) pain score less than or equal to 3 on a 10 score VAS scale; (iii) ability to straight leg raise; and (iv) ability to bend knee to 90 degrees. It will also be recorded whether patients were discharged, and if they were not discharged when fit for discharge the reasons for this will be collected.

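### Fitness for discharge is assessed only until first met, but it is analysed by a four-day repeated-measures logistic model with no rule for coding the later days

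*Combined protocol and SAP*

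**What the plan says.** Protocol 6.3 (Patient Participation) has fitness assessed as part of routine care on the evening of surgery and on "day 1, 2 and 3 following surgery, until the patient is deemed fit for discharge". For patients who go home within 72 hours, the same section provides a daily telephone call for pain, QoR-40 and, where appropriate, EQ-5D-5L. The call does not cover mobility, straight-leg raise or knee flexion. Protocol 8.5 likewise places the fitness assessment in the in-patient stage.

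SAP 6.1 gives the same schedule without the stopping clause: "this will be assessed against pre-defined criteria on evening of surgery (day 0) and days 1, 2, and 3 following surgery".

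SAP 6.2 (Secondary outcomes) then sets out the analysis:
- Model: "The two treatment groups will be compared using a multi-level logistic regression model with repeated measures (level 1) nested within participants (level 2", with centre as a random effect at level 3 and type of replacement, age and gender as fixed effects.
- Time: "Time will be included as a categorical covariate and a treatment-by-time interaction will be included".
- Results: "Adjusted ORs and associated 95% confidence intervals will be reported at each time point". Also, "Unadjusted ORs will also be calculated".
- Relapses: "Any instances where someone is fit for discharge at one time point and not at some subsequent one will be summarised".

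Time from surgery to fitness is only described, by medians and IQRs. SAP 6.3 (Missing Data) has a post-discharge imputation rule for pain scores but none for fitness.

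**The concern.** The model needs a fit or not-fit status for each patient on each of four days. Protocol 6.3 yields something else: a run of not-fit records that ends either at the first fit record or at day 3. The two can be joined only by a coding rule for the days after first fitness and after discharge, and there is none. The denominators for the daily percentages and unadjusted ORs in SAP Table 13 are undefined for the same reason.

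The protocol's background section gives earlier mobilisation and discharge as reasons for the trial, so readers will look at this outcome. The planned adjusted ORs could be arbitrary or absurd in size. On later days they could also be read as comparing all patients when they compare only the slower recoverers left in each arm.

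**Working it through.** **Inputs.** The documents give no fitness rates, effect size or power for this outcome, so there is no stated figure to reproduce. The arm size comes from SAP 3.3: 240/(1 - 0.04) = 250. All fitness rates below are assumptions. Centre and covariates are left out of the fits.

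**Main illustration.** Cumulative percentage fit on days 0/1/2/3: control 5/30/60/85, intervention 10/45/75/85.

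*OR of being fit by each day, all patients.* Formula: [i/(1 - i)] / [c/(1 - c)], where i and c are the cumulative proportions fit in the intervention and control arms.
- Day 0: (10/90)/(5/95) = 2.11
- Day 1: (45/55)/(30/70) = 1.91
- Day 2: (75/25)/(60/40) = 2.00
- Day 3: (85/15)/(85/15) = 1.00

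*OR among patients not yet fit.* Formula: newly fit over still not fit, intervention against control.
- Day 0: 2.11
- Day 1: (35/55)/(25/70) = 1.78
- Day 2: (30/25)/(30/40) = 1.60
- Day 3: (10/15)/(25/15) = 0.40

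On day 3 the second set rests on 250 × 0.40 = 100 control and 250 × 0.25 = 62.5 intervention patients.

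**Coding 1: later days missing.** Only five records are possible: 1; 0,1; 0,0,1; 0,0,0,1; 0,0,0,0. Two arms therefore supply 2 × (5 - 1) = 8 free proportions. The model already has 8 day-by-arm terms and adds a participant SD. For any SD, the 8 terms can reproduce the counts exactly, so the data carry no information on the SD. The saturated log-likelihood is 250 × Σ p ln p, summed over both arms:
- Control, p = 0.05, 0.25, 0.30, 0.25, 0.15: 250 × (-1.4887) = -372.17
- Intervention, p = 0.10, 0.35, 0.30, 0.10, 0.15: 250 × (-1.4737) = -368.43
- Total: -740.60

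The fitted value is -740.602 whatever the SD, but the ORs are not constant:

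| Participant SD | Day 0 | Day 1 | Day 2 | Day 3 |
|---|---|---|---|---|
| 0.01 | 2.11 | 1.78 | 1.60 | 0.40 |
| 0.5 | 2.14 | 1.86 | 1.71 | 0.41 |
| 2 | 2.73 | 2.81 | 2.85 | 0.47 |
| 5 | 6.93 | 8.31 | 9.31 | 0.65 |

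Software would report one of these rows according to where its optimiser stopped.

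**Coding 2: fitness carried forward.** Status never returns to not fit. Any finite SD predicts some returns, so the likelihood keeps rising with the SD. It was still rising at SD 30, where the ORs for days 0 to 2 were about 47,000 to 233,000. Only their order of magnitude means anything, because the values depend on the numerical integration. In the four scenarios below, the fitted SD was about 29 to 36.

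**Does the direction reverse?** This was checked in four further assumed scenarios:

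| Scenario | OR fit by days 0/1/2/3 | OR among those not yet fit |
|---|---|---|
| A: control 5/30/60/80, intervention 5/45/68/82 | 1.00/1.91/1.42/1.14 | 1.00/2.04/0.96/0.78 |
| B: same control, intervention 10/55/72/82 | 2.11/2.85/1.71/1.14 | 2.11/2.80/0.81/0.56 |
| C: constant daily OR of 1.5 | 1.50/1.53/1.67/1.93 | 1.50 on every day |
| D: participant SD 2, conditional OR of 2 | 1.66/1.55/1.57/1.64 | 1.66/1.46/1.36/1.29 |

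Days 2 and 3 reverse in A and B, where the intervention works early and control catches up. Nothing reverses in C or D. Even in A, the day 3 OR under Coding 1 runs from 0.78 at SD 0.01 to 1.28 at SD 5, with the log-likelihood fixed at -734.894.

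**The case against.** The strongest reply is that the SAP expects re-assessment on every day. It plans to summarise patients who are fit and later not fit, and Table 14 crosses fitness with discharge status on each of days 0 to 3. If every patient were examined on all four days, the objection would largely fall away. The stopping clause in protocol 6.3 says otherwise, however, and no schedule collects the physical criteria after discharge. Re-examining only patients who are fit but still in hospital would leave a selected group.

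A second reply is that an OR among patients not yet fit is a legitimate quantity. That stands: 0.40 on day 3 is correct for what it measures, 40% against 62.5% newly fit. Stopping at first fitness also depends only on observed data, and with the participant SD known the model recovers the conditional effect (2.0 on every day in scenario D). But the SD is not known. Covariates and centre, omitted here, would identify it only weakly and through model assumptions.

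A third reply is that the SAP also plans crude daily percentages and unadjusted ORs. If fitness is carried forward, these are correct as comparisons of fit by each day. The SAP does not choose that coding.

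A reader might infer that the model must show harm on later days, or must shrink a real benefit. Neither follows. Reversal needs post-fitness days treated as missing, together with control catch-up. As for shrinkage, at SD 2 in the main illustration the ORs for days 0 to 2 (2.73/2.81/2.85) exceed the cumulative ones (2.11/1.91/2.00).

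**Conclusion.** The concern holds as a mismatch between how the outcome is collected and how it is modelled. Under both natural codings the planned adjusted daily ORs cannot be used: under one they are essentially unidentified, and under the other they diverge. For the day-by-arm model without covariates, this follows from the form of the records, not from the assumed rates. The particular ORs, and any reversal, do depend on those rates.

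The point should be fixed, but its reach is limited. Fitness for discharge is one of several secondary outcomes, which SAP 4.1 treats as supporting. The co-primary analyses of QoR-40 and pain, and the sample size, are unaffected. The documents do not support reading this as a threat to the trial's main conclusion.

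**What to change.** 1. Reconcile protocol 6.3, SAP 6.1 and SAP 6.2 on whether assessment continues after first fitness.
2. State how days after first fitness and after discharge are coded, including for patients discharged before meeting all four criteria (a cell that Table 14 allows for). State the denominator for every row of Table 13.
3. Replace the repeated-measures logistic model with an analysis of day first fit (0, 1, 2, 3, not by day 3). An adjusted ordinal or discrete-time model with the planned covariates would serve. If a discrete-time model is used, state the at-risk set.
4. Check the common-effect assumption. It can fail: in the main illustration neither the cumulative ORs (2.11/1.91/2.00/1.00) nor those among patients not yet fit (2.11/1.78/1.60/0.40) are constant.
5. Report the cumulative proportion fit by each day, with adjusted single-day comparisons, over all randomised patients, or over all operated patients if that is stated.

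The cost is SAP wording and a simpler model, with no new data. The downside is that a single common effect may hide differences between days, which the cumulative daily figures keep visible.
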